## Abstract

**Background:**

Previous studies have shown that acupuncture can alleviate postmenopausal symptoms, such as hot flashes, but few studies have assessed symptoms during the menopausal transition (MT) period. Thus, the effect of acupuncture upon MT symptoms is unclear. We designed a large-scale trial aimed at evaluating the efficacy of electroacupuncture for MT symptoms compared with sham electroacupuncture and at observing the safety of electroacupuncture.

**Methods/design:**

In this multicenter randomized controlled trial, 360 women will be randomized to either an electroacupuncture group or a sham electroacupuncture group. During the 8-week-long treatment, a menopause rating scale, average 24-hour hot flash score, Menopause-Specific Quality of Life Questionnaire score, and level of female hormones will be observed. Follow-ups at the 20th and 32nd week will be made.

**Discussion:**

Though there is no completely inert placebo acupuncture and blinding is difficult in acupuncture trials, the placebo effect of EA can still be partially excluded in this study. For the placebo control, we use non-points and a tailor-made sham needle. This needle is different from a retractable needle, which is usually used for sham acupuncture. The needle in this trial is more simply constructed and more acceptable to Chinese people. We expect to evaluate the efficacy of electroacupuncture for MT symptoms and clarify its effect on these symptoms.

**Trial registration:**

ClinicalTrials.gov Identifier: NCT01849172 (Date of registration: 05/05/2013).

## Background

The menopausal transition (MT) period refers to the time from the commencement of variations in menstrual cycle length and a monotropic rise in follicle-stimulating hormone to the final menstrual period. It is further divided into two phases: the ‘early MT’ in which cycle lengths vary by more than 7 days from the typical length for the individual woman and the ‘late MT’ , characterized by at least two skipped cycles and at least one period of amenorrhea exceeding 60 days [1-4]. Different symptoms appear during different phases of the MT period. Hot flashes are the most frequent symptom and the prevalence of flashes can be as high as 79% at the completion of menopause [5,6]. Other symptoms include night sweats, sleep disturbances, vaginal dryness, urinary incontinence, weight gain, fatigue, irritability, and anxiety. Studies find that most women experience at least one or more of these symptoms as they transit through the postmenopausal stage of life [7].

Hormone therapy (HT) is the recommended drug for women with symptoms related to postmenopause [8]. Because of its long-term risks, HT is no longer prescribed as preventive therapy, but rather for managing menopausal symptoms [9]. Treatment of the perimenopausal woman represents a greater challenge than the menopausal woman because of unpredictable and unstable ovarian function [10]. A study of women’s decision making during the MT has shown that participants believe that menopausal symptoms are best managed with a natural product rather than HT [11].

As part of complementary and alternative medicine, acupuncture has been used in many clinical trials in recent years. Existing studies have shown that acupuncture can alleviate postmenopausal-related symptoms, but we were unable to find many trials on the MT period. A review of acupuncture for treating menopausal hot flashes included six randomized controlled trials (RCTs), which compared acupuncture with sham acupuncture, and they concluded that sham-controlled RCTs failed to show any specific effects of acupuncture for control of menopausal hot flashes [12]. Two trials conducted separately in the United States and South Korea on perimenopausal and postmenopausal women showed acupuncture was beneficial for hot flashes, though it was not more effective than sham acupuncture [13,14]. The limitations of the above two trials were that both trials had small samples (n = 103 and n = 175, respectively), they included both perimenopausal and postmenopausal women, treatment sessions were insufficient (one trial had 10 sessions in 5 weeks and the other 12 sessions in 4 weeks), and follow-up periods were short-term (7 weeks and 4 weeks). Another trial conducted in South Korea reached a similar conclusion that acupuncture failed to show significant effects on hot flash scores compared with sham acupuncture, but it showed partial benefits for hot flash severity [15]. Several trials [16-20] conducted in China demonstrated that electroacupuncture (EA) could reduce the Kupperman Index, follicle-stimulating hormone (FSH), and luteinizing hormone (LH), and increase estradiol (E2), but none of these trials used a sham control or had follow-up. In sum, most trials so far have focused on hot flashes in postmenopausal women and no significant differences were found between acupuncture and sham control. The few trials on MT-related symptoms showed that there was not enough evidence to support acupuncture’s efficacy for MT [21].

We have finished a phase I trial (unpublished), which was a single-blinded (patients blinded) RCT study; 16 women with MT-related symptoms were observed. They were randomized into an EA group (n = 8) and a sham EA group (n = 8). After 8 weeks, the reduction in the menopause rating scale (MRS) was 6.5 ± 9.96 (20.54 ± 14.82 at baseline and 14.00 ± 4.47 after treatment) and 2.00 ± 7.39 (21.50 ± 13.03 at baseline and 19.50 ± 7.85 after treatment) for the EA and sham EA groups, respectively. There was a significant difference between the two groups and the results suggested EA could be beneficial for MT symptoms and have a therapeutic effect.

This protocol is designed for the phase II trial. It is a multi-center randomized placebo controlled trial. It will compare EA with sham EA for symptoms during MT. The primary objective is to evaluate the therapeutic effect of EA for MT symptoms, and to partially exclude the placebo effect. The second objective is to evaluate EA’s safety and any positive effect on the sexual hormone levels (FSH, LH, FSH/LH, and E2) in MT.

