### Sample size and statistical analysis

According to our pilot trial, the reduction of MRS after an 8-week treatment was 6.5 ± 9.96 (mean ± standard deviation) and 2.00 ± 7.39 for the acupuncture and sham acupuncture groups, respectively. Considering it is a multicenter trial, we expanded the standard deviation to 1.5 times to enhance the reliability of the study. As a minimum 5-point reduction in MRS is considered effective [23], to detect a reduction of 5 points with a two-sided 5% significance level and a power of 95%, 180 participants will be needed for each group (1:1 ratio) allowing for a 20% dropout rate.

Data from the 12 hospitals will be pooled and the Clinical Evaluation Center of China Academy of Chinese Medical Sciences in Beijing will conduct a statistical analysis. According to the principle of intention-to-treat (ITT), all randomized participants will be analyzed. All statistical analyses will be two-sided tests and the level of significance will be established at 0.05. SAS 9.1.3 (SAS Institute, Cary, NC, USA) and SPSS Ver.13.0 (SPSS Inc., Chicago, IL, USA) software will be used. Continuous data will be represented by the mean, standard deviation, median, minimum value, and maximum value; categorical data will be represented by percentages. For comparison with the baseline, a *t*-test or nonparametric test will be used for continuous data, and nonparametric tests for categorical data. For comparison of two independent samples a *t*-test or nonparametric test will be used for continuous data, and a χ^2^ test or the Fisher exact test will be used for categorical data. The multiple imputation method will be used to handle the missing data. The statistical methods are as follows:

1. Case distribution and compliance analysis: case distribution of both groups in every center will be described. The total drop-out rate and the drop-out rate due to adverse events, of both groups, will be compared using the Fisher exact test.

2. Analysis of baseline characteristics.

3. Analysis of compliance: according to recordings in the case report form, compliance of the two groups will be compared.

4. Analysis of efficiency: efficiency analysis will be based on the ITT population (all randomized participants). Subjects without any treatment after randomization or without any valid data of evaluation although treated will still be included in the analysis.

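### The three pilot SDs reported for the electroacupuncture arm cannot all be right, one of them feeds the sample size, and the pilot's significance statement is not supported by the reported reductions

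*Protocol article*

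**What the plan says.** The Background describes an unpublished pilot of 16 women: "They were randomized into an EA group (n = 8) and a sham EA group (n = 8"). For EA it reports a reduction in MRS at 8 weeks of 6.5 with SD 9.96 ("20.54 ± 14.82 at baseline and 14.00 ± 4.47 after treatment"), and for sham "2.00 ± 7.39 (21.50 ± 13.03 at baseline and 19.50 ± 7.85 after treatment"). It then states: "There was a significant difference between the two groups". No test or p value is given.

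The section on sample size and statistical analysis carries the same reductions forward as "6.5 ± 9.96 (mean ± standard deviation) and 2.00 ± 7.39 for the acupuncture and sham acupuncture groups", which settles that the ± figures are standard deviations. It multiplies the SDs by 1.5 because the trial is multicentre. It then asks for 95% power at a two-sided 5% level to detect 5 points, and arrives at 180 per group, said to allow for 20% dropout.

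**The concern.** Baseline, post-treatment and change scores from the same women are tied together algebraically: the SD of change depends only on the other two SDs and their correlation. The three EA values break that relation. The change SD is also the larger of the two SDs behind the 180 per group and supplies most of the variance. If it is understated, so is the sample size.

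The second issue is the sentence on significance. It comes straight after the two reductions, and the pilot is used there as evidence of a therapeutic effect. With 8 women per arm and SDs of 7 to 10 points, a difference of 4.5 points does not look significant.

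**Working it through.** **Inputs.** From the Background: EA baseline 20.54 (SD 14.82), post-treatment 14.00 (SD 4.47), change 6.5 (SD 9.96); sham 21.50 (13.03), 19.50 (7.85), 2.00 (7.39); 8 per arm. From the sample size section: factor 1.5, difference 5, two-sided 5%, power 95%, 180 per group.

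**1. The plan's own figure.** n per group = (SD₁² + SD₂²)(1.960 + 1.645)² / 5². The inflated SDs are 1.5 × 9.96 = 14.94 and 1.5 × 7.39 = 11.085, with squares summing to 346.08. So n = 346.08 × 12.995 / 25 = 179.9, or 180. This reproduces 180 as the number *before* dropout. With 20% dropout, 180 × 0.8 = 144 remain, and power is 89.7% on the plan's own SDs. That shortfall is a separate problem. The 9.96 supplies 9.96² / (9.96² + 7.39²) = 64.5% of the variance sum.

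**2. Consistency of the SDs.** For paired data, SD(change)² = SDb² + SDp² − 2r·SDb·SDp, so r = (SDb² + SDp² − SDc²) / (2·SDb·SDp).
- EA: (219.63 + 19.98 − 99.20) / 132.49 = 1.06, which is impossible. The minimum change SD, at r = 1, is 14.82 − 4.47 = 10.35. The most favourable rounding gives 14.815 − 4.475 = 10.34, still above 9.96.
- Sham: (169.78 + 61.62 − 54.61) / 204.57 = 0.864, which is feasible.

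Changing any one EA figure can restore consistency: a change SD of at least 10.35, a baseline SD of at most 9.96 + 4.47 = 14.43, or a post-treatment SD of at least 14.82 − 9.96 = 4.86.

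**3. Effect on power if 14.82 and 4.47 are right.** The EA correlation is not reported, so each r below is an assumption. The factor 1.5 and the sham SD are kept.

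| EA change SD | Evaluable n per group for 95% power | Power at 180 | Power at 144 |
|---|---|---|---|
| 9.96 (as reported) | 180 | 95.0% | 89.7% |
| 10.35 (r = 1, the minimum) | 190 | 94.0% | 88.2% |
| 11.19 (r = 0.864, as implied in sham) | 211 | 91.6% | 84.7% |
| 13.17 (r = 0.5) | 267 | 84.2% | 75.5% |

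**4. The pilot comparison.** Change: difference 6.5 − 2.0 = 4.5; SE = √(9.96²/8 + 7.39²/8) = 4.385; t = 1.03 on 14 df; p = 0.32; 95% CI 4.5 ± 2.145 × 4.385 = −4.9 to 13.9. Post-treatment: difference 5.5; SE = √(4.47²/8 + 7.85²/8) = 3.194; t = 1.72; p = 0.11.

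**5. A baseline-adjusted test.** This cannot be computed from inconsistent figures, but it can be bracketed by taking the baseline and post-treatment SDs as right, r = 0.864 in sham and an assumed r in EA. With r = 0.864 in EA, the pooled within-arm sums are Sxx = 2725.9, Syy = 571.2 and Sxy = 1019.3. The slope is 1019.3 / 2725.9 = 0.374. The adjusted difference is −5.5 + 0.374 × 0.96 = −5.14. The residual variance is (571.2 − 1019.3²/2725.9) / 13 = 14.62, and the SE is 1.913. So t = 2.69 and p = 0.019. With r = 1 in EA, p = 0.008; with r = 0.5, p = 0.052.

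**The case against.** **A reader might infer that 9.96 is the wrong figure and that the error flatters the design.** The document does not show this. If the slip is in 14.82 or 4.47, then 9.96 stands and so does the variance behind 180. A baseline SD only about 0.4 lower would be enough. The baseline and post-treatment means also differ by 6.54, not 6.5; that may be rounding and does not identify the error.

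**The guaranteed effect is small.** Even if 9.96 is wrong, the certain loss is about one percentage point of power at 180 and about 5% more women (190 against 180). The larger losses rest on assumed correlations, and 0.5 has no source in the document. Most of the gap below 95% at 144 comes from the dropout allowance, not from this SD. The factor of 1.5 cushions the error: the planning SD of 14.94 exceeds 10.35, 11.19 and 13.17. All of this stands, except that the factor was introduced for variation between centres, so using it to absorb a pilot error leaves less for its stated purpose.

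**A reader might also infer that the pilot difference was not significant under any analysis.** That goes too far. No test is named, and the main trial plans analysis of covariance for its primary outcome. At feasible correlations such an analysis gives p between about 0.008 and 0.05. The reported reductions fail to support the statement, but they do not disprove it.

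**The bound assumes the same 8 women contribute to all three figures.** The Background gives n = 8 and mentions no missing data. If different women contributed, that would itself need stating.

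**Conclusion.** The point holds in two limited parts. First, the EA-arm baseline, post-treatment and change SDs are mutually inconsistent, given the same 8 women at both visits. Rounding does not rescue them, and at least one is wrong. Whether the sample size is affected depends on which. If the change SD is the wrong one, the loss of power at 180 per group is at least one point (95.0% to 94.0%), and several points more if the correlation is well below 1. If it is one of the other two, the power is unaffected and only the Background needs correcting.

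Second, the statement of a significant pilot difference is unsupported by the unadjusted reductions (p = 0.32) and by the post-treatment scores (p = 0.11). It may rest on an adjusted analysis that the document does not describe.

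**What to change.** Recompute the three EA-arm SDs and the mean change from the pilot records, and state how many women contribute to each. Correct the Background and, if the change SD moves, the sample size section as well. In that case restate the power at 180 and at 144 evaluable per group with the corrected SD.

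For the pilot comparison, name the test used and report its estimate, confidence interval and p value from the corrected data, or withdraw the statement. The figure p = 0.32 should not be written in as the replacement, because it uses an SD that is itself in doubt.

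The cost is a recheck of 16 existing records and a few lines of text. The check itself adds no participants, though the stated power may come out lower.

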## Methods/design

This will be a prospective RCT conducted over 2 years (from June 2013–May 2015) and at 12 hospitals in China (Guang’anmen Hospital; The First Hospital Affiliated to Anhui University of Chinese Medicine; Guangdong Provincial Hospital of Traditional Chinese Medicine (TCM); Hubei Province Hospital of TCM; The First Hospital of Hunan University of Chinese Medicine; Hengyang Hospital of Hunan University of Chinese Medicine; Affiliated Hospital of Shandong University of TCM; Integrated TCM and Western Medicine of Shanxi University of TCM; Shanxi Province Hospital of TCM; Yueyang Hospital of Shanghai University of TCM; TCM Hospital of Yantai; and 3rd Hospital of Zhejiang Chinese Medical University).Participants experiencing MT will be recruited from the 12 centers by use of advertisements in newspapers, television, websites, and posters. Participants will be sent to a gynecologist who will make the diagnosis. A 1-week baseline assessment will include MRS, Menopause-Specific Quality of Life Questionnaire score (MENQOL), average 24-h hot flash score, and hormone levels (FSH, LH, FSH/LH, and E2, examined at days 2 to 4 of the menstrual period or any day for participants in menopause). Eligible participants will be randomized after their informed consents are obtained. Central randomization will be performed by the Clinical Evaluation Center of the China Academy of Chinese Medical Sciences in Beijing. Stratified block randomization will be made according to the hospital and a block size of six will be used. A random number will be immediately received by the acupuncturist by phone or online after the informed consent is signed. All of the participants, statisticians, outcome assessors, and the gynecologists are blinded to the allocation, except for the acupuncturists. The flowchart of the trial is presented in Figure 1.

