### Participants

In total, 360 participants will be recruited in this trial.

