## Trial status

The first participant was included on 9 June 2013. To date, 80 participants have been recruited.

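### A single, published block size of six within each hospital lets an unblinded acupuncturist who sees every allocation there know up to 25% of assignments in advance

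*Protocol article*

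**What the plan says.** The Methods/design section of the protocol article describes central randomization run from Beijing and fixes the scheme: "Stratified block randomization will be made according to the hospital and a block size of six will be used". It mentions no variation in block size and no withholding of the size from the centers. On delivery of the allocation it says: "A random number will be immediately received by the acupuncturist by phone or online after the informed consent is signed". On blinding it says: "All of the participants, statisticians, outcome assessors, and the gynecologists are blinded to the allocation, except for the acupuncturists".

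The same section has a gynecologist make the diagnosis, includes a 1-week baseline assessment, and randomizes eligible women after consent. The ratio is 1:1 (Sample size and statistical analysis), and 360 women are to be recruited at 12 centers. The Interventions section speaks of acupuncturists in the plural but does not say how many work at each hospital. At the time of writing, the Trial status section reports: "To date, 80 participants have been recruited".

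**The concern.** Central randomization hides the list, but it does not stop anyone who knows past allocations from working out the end of a block whose size is fixed and known. Here the size is in print during recruitment. Each hospital runs its own sequence, so only local allocations need to be tracked. Acupuncturists deliver the real or sham treatment, so they necessarily know which arm each of their participants is in.

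If someone at a center knows or can guess the next arm and can also affect who is put forward or when, the arms may differ before treatment begins. Blinding participants and assessors after allocation does not protect against that. The trial has some exposure: the inclusion criteria give menopausal transition symptoms by example, with no minimum score, and the primary outcome is change on a symptom scale. The planned analysis of covariance could adjust for measured baseline differences, but not for selection on unmeasured traits such as expectation of benefit.

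**Working it through.** The article states no predictability figure, so there is none to reproduce.

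**Inputs.** Block size 6, stratified by hospital (Methods/design). Ratio 1:1, so three of each arm per block (Sample size and statistical analysis). 360 participants (Participants), 12 hospitals (Methods/design), 80 recruited (Trial status), hence 360 − 80 = 280 remaining.

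**Assignments known with certainty.** An assignment is forced once one arm has used its three places in the block. There are C(6,3) = 20 equally likely block orders:

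- 12 orders have 1 forced assignment, 6 have 2, and 2 have 3.
- Mean: (12×1 + 6×2 + 2×3)/20 = 30/20 = 1.5 per block, which is 1.5/6 = 25%.
- The closed form for a block of 2m gives the same: 2m/(m+1) = 6/4 = 1.5 with m = 3.
- By position, the chance of being forced is 0% for places 1 to 3, 10% for place 4, 40% for place 5 and 100% for place 6.

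Over the whole trial this is 60 blocks × 1.5 = 90 of 360. Over the remaining allocations it is 0.25 × 280 = 70. If hospitals recruit equally (an assumption), each has 360/12 = 30 participants, or five blocks, with 5 × 1.5 = 7.5 forced assignments. Incomplete final blocks lower these figures slightly.

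**Best guess.** Always guessing the arm with more places left is right with probability 0.5, 0.6, 0.6, 0.7, 0.7 and 1.0 at places 1 to 6. The sum is 4.1 of 6, or 68.3%, against 50% by chance.

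**Dependence on who sees what.** The 25% needs one person with all of the hospital's allocations. If k acupuncturists share cases at random and pool nothing, the one treating the next participant must have personally treated all three in the exhausted arm. This has probability (1/k)³:

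| Acupuncturists per hospital, no pooling | Forced assignments |
|---|---|
| 1 (or several who pool) | 25% |
| 2 | 25% × 1/8 = 3.1% |
| 3 | 25% × 1/27 = 0.9% |

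Simulation agrees (25.0%, 3.2%, 0.9%).

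**Effect of varying the block size.** Simulation with 30 participants per hospital, sizes equally likely, and an observer who sees every allocation and knows the set of sizes but not their order:

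| Block sizes | Known with certainty | Best guess correct |
|---|---|---|
| 6 only | 25% | 68% |
| 4, 6 | 6% | 69% |
| 4, 6, 8 | 2% | 67% |

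Varying the size removes most of the certainty and leaves the guess rate almost unchanged.

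**The case against.** The strongest reply is that predictability alone harms nothing without a route into enrolment, and the article describes safeguards on that route. A blinded gynecologist makes the diagnosis, baseline is assessed over a week, and the number is released only after consent. Nothing in the text gives the acupuncturist authority over eligibility, consent or timing. The article says that the acupuncturist receives the number, not who asks for it. This stands, and it limits the point to a weakness of degree. Who takes consent and schedules enrolment is the sort of detail that a condensed article leaves to the full protocol, so its absence is not counted against the plan.

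It is also fair that 25% is an upper figure. The plural in the Interventions section suggests that more than one acupuncturist may work at a hospital, in which case any one of them may know far less. However, nothing in the article says that colleagues in the same hospital keep their allocations from one another, so the upper figure cannot be dismissed.

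Finally, varying the block size hardly changes the best-guess rate. That is correct, and the change should be recommended for removing certain knowledge only.

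What the reply does not answer is that one known block size is a stated design rule, and that central concealment of the list does not prevent deduction from it.

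**Conclusion.** The point stands as an avoidable weakness in allocation concealment that is cheap to reduce. Between about 1% and 25% of assignments can be known in advance. The upper end applies if one acupuncturist sees all of a hospital's allocations or several pool them, and if the start of each block is tracked. The figures of about 3% and 1% apply if two or three share cases at random without pooling. For the 280 participants remaining at the time of writing, the upper end is about 70. Fewer are at stake if recruitment had moved on by the time of publication.

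A reader might infer two stronger things. One is that a quarter of assignments are in fact predictable at every center. The document does not support this, because it does not give the number of acupuncturists per hospital or say what they share. The other is that the comparison of electroacupuncture with sham is biased, or would be. The document does not support this either: harm requires that center staff who know past allocations can influence who is enrolled or when, and the described steps put diagnosis with a blinded clinician and release after consent.

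**What to change.** For the remaining allocations, have the Clinical Evaluation Center generate the hospital-stratified lists with randomly varying block sizes, for example 4, 6 and 8, and not disclose the sizes to the centers. Under the least favorable assumption about shared knowledge, certain knowledge falls from 25% to about 2%, or from about 70 to about 6 of 280 (0.02 × 280 = 5.6). Best-guess accuracy stays near 67%.

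No new rule on the timing of release is needed for this purpose, since randomization after eligibility and consent is already planned.

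The cost is central work on 12 lists, plus a small imbalance in each hospital's final block and in any block open at the switch. An open block can be completed, in which case its last places stay predictable, or abandoned, in which case its imbalance remains. Either choice should be made once and recorded.
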